#### Intervention

After completion of the screening day, participants will visit the hospital on a weekly basis, for 10 consecutive weeks. Treatments and in-hospital assessments will be conducted in the practically-defined OFF phase and will therefore commence in the morning. The treatment session in the OFF state is preceded by a baseline clinical assessment and is immediately followed by a post-intervention clinical assessment and an assessment after 30 min (Table 3). The intervention is administered in a hospital by an experienced lab technician, who also continuously monitors participants during and after the intervention. During the intervention, the inhaled FiO2 is measured continuously using the COSMED® metabolic system (*Quark CPET* metabolic cart for cardiopulmonary testing, COSMED Srl, The Metabolic Company, Italy), which also measures peripheral oxygen saturation, blood pressure, respiratory rate and tidal volume. In addition, the subjective participant experience regarding dizziness, discomfort and stress is registered by the lab technician during the intervention. In addition, to maximize safety of the participants during the intervention, clear stopping criteria are defined. If these are met, the lab technician will halt the intervention (‘Stopping Criteria’, Supplementary Materials).

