### Outcomes and measurements

#### Primary outcomes

The main primary outcomes of this study are the safety and feasibility of IHT under well-controlled circumstances in a lab-based setting. Safety outcomes will be measured by the lab technician during the intervention and by the reporting of adverse events. The feasibility questionnaire (Supplementary Table 3) is designed together with a patient researcher. The questionnaire’s content is based on the main categories from a widely used feasibility framework [49]. Statements in every category (e.g. acceptability, expectancy) were subsequently inspired by previously published healthcare feasibility questionnaires. Primary outcomes are summarized in Table 2.

**Table 2 Tab2:** Primary outcomes

**Primary outcome variable**	*Measurement frequency*
Nature and number of adverse events	Every 10 min during intervention, up to one hour post-intervention, one time next morning post-intervention
Self-reported dizziness, discomfort and stress on a ten-point scale	Every 10 min up to one hour post-intervention, one time next morning post-intervention
Number of serious or irreversible adverse events	Every 10 min, up to one hour post-intervention, one time next morning post-intervention
	*Measured continuously for safety, recorded:*
- Blood pressure systolic-diastolic	Baseline and every 5 min—> 30 min post-intervention
- Heartrate	Baseline and every 5 min—> 30 min post-intervention
- Respiratory rate	Baseline and every 5 min—> 30 min post-intervention
- Oxygen saturation	Baseline and every 5 min—> 30 min post-intervention
Feasibility questionnaire (total score and subscores) (in *Supplementary Materials*)	After 1^st^, 5^th^ and 10^th^ intervention

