#### Analysis of primary study parameters

Safety outcomes will be analyzed using descriptive statistics of total number and percentages of adverse events, number of serious reversible or irreversible adverse events and vital parameters. Feasibility outcomes will be analyzed using descriptive statistics of feasibility outcomes including the feasibility questionnaire sum score and domain-specific scores.

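### Table 2 defines the primary vital-sign safety outcomes as 5-minute readings of continuously measured signals; also reporting each session's lowest saturation would close a small, one-directional gap

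*Protocol article*

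**What the plan says.** In the protocol article, Table 2 (Primary outcomes) lists blood pressure, heart rate, respiratory rate and oxygen saturation as primary outcome variables. Its heading for the four is "Measured continuously for safety, recorded" and the schedule for each is "Baseline and every 5 min—> 30 min post-intervention". Adverse events are separate primary outcomes with their own schedule: "Every 10 min during intervention, up to one hour post-intervention, one time next morning post-intervention".

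The section on analysis of primary study parameters says that safety will be described by counts and percentages of adverse events, together with the "number of serious reversible or irreversible adverse events and vital parameters". It names no summary of a session, such as a minimum or a mean.

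The Intervention section under Study procedures describes the metabolic cart, "which also measures peripheral oxygen saturation, blood pressure, respiratory rate and tidal volume", and the technician, "who also continuously monitors participants during and after the intervention". On the stop criteria it says: "If these are met, the lab technician will halt the intervention". The criteria themselves and the detailed measurement scheme are in supplements that are not at hand.

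The Intervention section that lists the regimens gives 45 minutes of continuous hypoxia, or five 5-minute hypoxic bouts separated by 5-minute normoxic recoveries.

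**The concern.** In a first safety study of hypoxia in this population, readers will want to know how low saturation went in each session. Table 2 answers with its value at fixed clock times. A minimum taken over a few fixed times can err in one direction only, towards a higher saturation and so a safer appearance.

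Three things are at stake, all in the description of safety:

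- Brief dips will often fall between marks.
- If a session is halted between marks, the value that triggered the halt need not be in the listed outcome. For a halt at minute 12, the last scheduled reading before it is at minute 10.
- In intermittent sessions the marks coincide with the gas switches, and Table 2 does not say whether a reading comes before or after the switch.

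The data safety monitoring board's first interim analysis uses the safety outcomes, so the limitation would reach that review as well as the final report.

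**Working it through.** The article gives no figure for this outcome to reproduce. The check is a count from the stated grid, followed by illustrations on stated assumptions.

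**1. Readings per session.** Baseline 1; in session 45 / 5 = 9; afterwards 30 / 5 = 6; total 16.

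**2. Direction.** The nine readings are a subset of the signal, so min(readings) ≥ min(signal). This is exact for the minimum of the signal itself. Against a smoothed minimum, such as a 30-second mean, it need not hold in every session.

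**3. Short dips.** A dip of d seconds at a random time is caught by a 300-second grid with probability d / 300: 10 s gives 3%, 30 s gives 10%, 60 s gives 20% and 120 s gives 40%.

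**4. No short-term fluctuation.** Assume a 12-point fall, a time constant of 30 to 120 s, a delay of 0 to 30 s and readings exactly on the marks. The lowest reading then misses the minimum by 0 points in continuous sessions and by at most 0.3 points in intermittent sessions.

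**5. With fluctuation.** Assumptions, none from the article: a fall of 6 or 15 points, time constant 60 s, delay 15 s, autocorrelated fluctuation with SD 1 to 3 points and correlation time 20 to 180 s, readings exactly on the marks, and the minimum of a 5-second trace as the reference. Ranges run over the falls and correlation times (3,000 simulated sessions per setting).

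| Assumed SD (points) | Continuous: mean gap | Continuous: share with gap ≥ 2 points | Intermittent: mean gap | Intermittent: share with gap ≥ 2 points |
|---|---|---|---|---|
| 1 | 0.8 to 1.4 | 1% to 19% | 0.5 to 1.2 | 0% to 14% |
| 2 | 1.7 to 2.8 | 34% to 73% | 1.2 to 2.7 | 17% to 67% |
| 3 | 2.5 to 4.3 | 61% to 86% | 1.9 to 4.1 | 40% to 83% |

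A second simulation used the minimum of the 30-second mean as reference, with a 12-point fall, time constant 1.5 to 3 min, delay 0.5 min, correlation time 1 min and readings within 0.5 min of schedule. For SD 1, 2 and 3 it gave mean gaps of 0.9, 1.8 and 2.7 points in continuous sessions, and 0.5 to 0.6, 1.1 to 1.2 and 1.9 to 2.0 points in intermittent sessions. A repeat run on these settings came out 0.1 to 0.4 points lower, so these are orders of magnitude only.

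**6. Gas switches.** The intermittent session lasts 5 × 5 + 4 × 5 = 45 min. Bouts end at 5, 15, 25, 35 and 45 min and recoveries end at 10, 20, 30 and 40 min, so every switch is on a mark. With the 15 s delay and 60 s time constant of step 5, a reading s seconds after the end of a bout (s ≥ 15) shows exp(−(s − 15) / 60) of the peak fall:

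- s = 15: exp(0) = 100%
- s = 30: exp(−0.25) = 78%
- s = 60: exp(−0.75) = 47%

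A reading on the mark, or a few seconds late, is close to the low point. A habit of switching first and recording half a minute or more later would lose part of the fall in every bout.

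**The case against.** The strongest reply is that this is a reporting choice and that nothing in the article is wrong. The article does not say that the continuous trace is discarded. Table 3 lists heart-rate variability from RR intervals during the intervention, which needs a stored beat-level signal, so the 5-minute grid may not be all that is kept. Which summary to tabulate is often left to the full protocol or analysis plan. This stands in part: there is no contradiction and no false figure. But Table 2 does state a recording rule for a primary outcome, and that rule can be improved as written.

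A reader might infer that the lowest value is systematically missed. The documents do not support that. A sustained plateau is captured in continuous sessions, and in intermittent sessions the marks fall near the expected low points. Without fluctuation the gap is about 0. The non-trivial sizes come wholly from an assumed SD, and any part of that SD that is sensor noise is not true desaturation.

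A reader might also infer that participants are less protected. They are not: halting acts on live values, and adverse events are separate primary outcomes.

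Finally, a reader might conclude that continuous and intermittent regimens cannot be compared fairly. That does not follow. Setting by setting in step 5, the mean gap is only about 0.2 to 0.7 points smaller in intermittent sessions, and no formal safety comparison between regimens is planned. Reading times may distort such a comparison; they do not rule it out.

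**Conclusion.** The point holds as a low-cost improvement to the safety description. It is neither an error nor a contradiction. As listed, the primary saturation outcome can err only towards looking safer relative to the session minimum, and a value that triggers a halt between marks need not appear in it. The size cannot be fixed from the article: about 0 without short-term fluctuation, and roughly 0.5 to 4 points on average under assumed SDs of 1 to 3 points. The effect of the gas switch depends on a recording habit that Table 2 leaves open and on assumed response kinetics. The conclusion also assumes that the supplements do not already provide for a session minimum.

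**What to change.** Amend Table 2 and the analysis of primary study parameters as follows:

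- From the continuous signal, store for each session the lowest saturation (for example the lowest 30-second mean after artefact removal) and the highest heart rate, and describe both by condition.
- For any session halted early, record the vital signs and the time at the halt.
- Keep the 5-minute readings as the time course. In intermittent sessions take each at a fixed moment relative to the valve switch and label it hypoxic or normoxic.

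Time spent below the stop level is not a useful addition: the stop criteria are not in the article, and halting would itself cut that time short.

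The cost is exporting the signal, agreeing an artefact rule in advance and deriving a few variables. No new measurement or visit is needed.

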### Secondary outcomes

#### Self-reported outcomes

In this exploratory study, we will use a battery of outcomes to determine which symptoms or signs might respond to hypoxia. In accordance with accepted N-of-1 trial design recommendations and previously conducted trials [32, 50, 51], we have chosen to predefine personalized (self-reported) outcomes for each individual, scored on a 10-point Likert scale. Contrary to standardized PD scales, these outcomes better reflect important effects for the individual, and are potentially more sensitive to subtle treatment effects, reducing the risk of type II errors. Therefore, we included three participant-rated outcomes that assess on a 10-point Likert scale (allowing half points) general symptom impression, the urge to take a next dose of dopaminergic medication and the effect on one specific symptom that participants can choose themselves, based on goal attainment scale principles (Table 3). This symptom must fulfill the following criteria: it must fluctuate in severity throughout the day or between days, changes in its severity should be swiftly apparent and, if applicable, it is a symptom that previously improved at high altitude. To ensure a baseline score on these outcomes, participants will report these on a daily basis in the morning (in OFF) during the baseline period, i.e. 7 days preceding the start of the intervention period. On intervention days, participants will report these self-reported outcomes pre-intervention, directly post-intervention, 30 min post-intervention and from that moment on, another five times, on an hourly basis. In addition, these will be measured once every morning (i.e. in OFF) for the next three mornings after the intervention.

**Table 3 Tab3:** Secondary outcomes

Self-reported outcome variable	Researcher	Participant	Moment of measurement (in addition to baseline)	Measurement unit
**General symptom impression**		X	Directly after intervention and post-intervention 30 min, 1 h, 2 h, 3 h, 4 h and 5 h, and once every morning on the next three days	10-point Likert scale allowing half points
**Urge for dopaminergic medication** on the usual moments of intake		X	Directly after intervention and post-intervention 30 min, 1 h, 2 h, 3 h, 4 h and 5 h, and once every morning on the next three days	10-point Likert scale allowing half points
**Participant-selected symptom** (goal attainment scale)		X	Directly after intervention and post-intervention 30 min, 1 h, 2 h, 3 h, 4 h and 5 h, and once every morning on the next three days	10-point Likert scale allowing half points
**Motor symptom severity** (self-selected, symptom that improved most during high altitude exposure, if applicable)		X	Directly after intervention and post-intervention 30 min, 1 h, 2 h, 3 h, 4 h and 5 h, and once every morning on the next three days	10-point Likert scale allowing half points
**Motor symptoms** MDS-UPDRS part III	X		30 min post-intervention	Total score and subscores
**Hand tremor** Accelerometry/gyroscope	X		Directly post-intervention, 30 min post-intervention	Amplitude
**Rapid alternating movements** Accelerometry/gyroscope	X		30 min post-intervention	Amplitude
**Bradykinesia** Modified Perdue pegboard test	X		30 min post-intervention	Number of pins
**Gait** Timed Up & Go Test	X		30 min post-intervention	Steps and seconds
**Balance** MiniBESTest	X		30 min post-intervention	Total score and subscores
**Non-motor symptoms** MDS Non-motor Scale symptoms	X		30 min post-intervention	10-point Likert scale (half points)
**Stress** Heartrate variability	X		During intervention, directly after intervention, 30 min post-intervention	RR interval

The measurement scheme of all outcomes is displayed in Supplementary Fig. 1. Patients will report all self-reported outcomes digitally.

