#### Assessor-rated outcomes

Assessor-rated outcomes are summarized in Table 3. These consist of gold-standard general motor tests (Movement Disorders Society Universal Parkinson’s Disease Rating Scale part III, or MDS-UPDRS part III) and non-motor tests (symptoms from the MDS Non-motor symptoms scale, or NMSS), supplemented with specific tests for bradykinesia (Purdue pegboard test [52]), gait (Timed Up & Go Test [53]), balance (Mini-BESTest [54]) and quantified versions of the UPDRS items on tremor and pronation-supination (performed using accelerometry). These secondary outcomes are measured 30 min post-intervention, after which hypoxic preconditioning is believed to have its initial first window effects peak. After 30 min, the acute effects of hypoxia therapy peak, as shown in people with a cervical spinal cord injury [55], with the second window only occurring approximately 3 h post-intervention.

Various selected outcomes, including the UPDRS part III, are sensitive to the Hawthorne effect: individuals with PD try to perform as good as possible due to the awareness of being observed. To mitigate such effects, the placebo condition is added, for which the multiple N-of-1 design is also particularly suited [31, 36, 56].

Baseline characteristics that will be collected include age, gender, H&Y, quality of life (Parkinson’s disease questionnaire 39 [57]) and other medication. Potential effect modifiers include levodopa-equivalent dose (LED), sleep quality (4-point ordinal scale) and physical activity (International Physical Activity Questionnaire – Short Form, IPAQ-SF [58]) and these will be measured during every pre-intervention phase.

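### The effectiveness rule compares scores after treatment with an OFF baseline without fixing the rating times; if the 1–5 h self-ratings enter it, a resumed dopaminergic dose can be counted as a hypoxia effect

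*Protocol article*

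**What the plan says.** **Medication state by rating time.** Under Study procedures, Intervention, the article says: "Treatments and in-hospital assessments will be conducted in the practically-defined OFF phase and will therefore commence in the morning". The session is "immediately followed by a post-intervention clinical assessment and an assessment after 30 min", and no later hospital assessment is described there. Under Self-reported outcomes, the seven baseline mornings are labelled OFF, and so are the later ones: "once every morning (i.e. in OFF) for the next three mornings after the intervention". Between these come the same-day ratings, "another five times, on an hourly basis", with no medication state given.

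**Rating times.** For each participant-rated outcome, Table 3 lists seven same-day ratings (directly after the session, at 30 min, and at 1, 2, 3, 4 and 5 h) and one rating on each of three later mornings, ten in all. (Read literally, the text counts the hourly ratings from the 30 min point, which gives 1.5–5.5 h; Table 3 gives 1–5 h.) The urge-for-medication item is qualified as "on the usual moments of intake" and is rated at all these times.

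**Decision rule.** Under Bayesian analysis, every secondary outcome on the 10-point Likert scale is modelled. A treatment is effective if the posterior probability of a 0.75-point difference between the score after treatment and at baseline exceeds 80%, and ineffective if it is below 20%. The baseline is that day's pre-intervention measurement, hence OFF. The rule names no rating time and does not subtract placebo.

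**Adjustment.** Levodopa-equivalent dose is measured in each pre-intervention phase (Assessor-rated outcomes) and can enter one additional covariate analysis.

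**The concern.** A before-after rule attributes to the session everything that changes between the two measurements. Between the OFF baseline and a rating 1–5 h later, one thing that may change is that the participant has taken the usual dopaminergic medication. The urge item suggests that usual intake moments fall within the rating schedule, and OFF sessions start in the morning. If so, part of the measured change is a drug effect, and it would appear after placebo sessions as well as active ones. A levodopa-equivalent dose recorded before the session cannot describe a dose taken after it.

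A placebo contrast would not settle everything. The trial measures urge because it may respond to hypoxia. If hypoxia lowers the urge and intake is delayed, fewer ratings are medicated after active sessions than after placebo, and the contrast is diluted.

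What is at stake is the efficacy verdict, not the primary safety and feasibility outcomes. The window includes the later effect that the article describes, "with the second window only occurring approximately 3 h post-intervention". The Sample size section says that effect sizes and SDs of protocols found clinically meaningful will feed the power simulation for a follow-up study, so an inflated change would be carried forward.

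**Working it through.** The article gives no figure to reproduce here; it states that no formal sample size calculation can be performed. The check applies its rule to a protocol with no hypoxia effect.

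**Inputs from the article**
- Threshold 0.75 points; posterior probability above 80% (Bayesian analysis).
- Two sessions per protocol per participant (Intervention) and 20 participants, so 20 × 2 = 40 sessions per protocol.
- Post-session ratings per outcome: 2 (direct, 30 min) + 5 (hourly) + 3 (mornings) = 10, of which 7 are on the same day.

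**Assumptions, not in the article**
- A resumed dose improves the score by 1.5 points in each of the five hourly ratings and in no other rating.
- SD of the session change is 1.0–1.5 points, whichever ratings are averaged.
- Flat prior, known SD, independent sessions; between-person variance is ignored at group level.

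**Formula.** With SE = SD/√n, the rule fires when the mean change exceeds 0.75 + 0.8416 × SE. For a true mean change m,

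P(effective) = Φ((m − 0.75)/SE − 0.8416).

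SE is 0.707 (SD 1.0) or 1.061 (SD 1.5) for an individual (n = 2), and 0.158 or 0.237 for the group (n = 40).

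**Mean change m, by ratings used**
- All ten: 1.5 × 5/10 = 0.75
- Seven same-day: 1.5 × 5/7 = 1.071
- 1–5 h only: 1.5
- OFF ratings only: 0

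| Ratings used | m | Individual, SD 1.0 / 1.5 | Group, SD 1.0 / 1.5 |
|---|---|---|---|
| All ten | 0.75 | 0.20 / 0.20 | 0.20 / 0.20 |
| Seven same-day | 1.071 | 0.349 / 0.295 | 0.883 / 0.696 |
| 1–5 h only | 1.5 | 0.587 / 0.447 | 1.000 / 0.990 |
| OFF only | 0 | 0.029 / 0.061 | 0.000 / 0.000 |

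Worked case (seven same-day ratings, individual, SD 1.0): (1.071 − 0.75)/0.707 − 0.8416 = 0.455 − 0.842 = −0.387, and Φ(−0.387) = 0.349.

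**Placebo contrast with equal intake.** The medication gain cancels, so m = 0 and the SE grows by √2. For an individual at SD 1.0, Φ(−0.75/1.0 − 0.8416) = 0.056; at SD 1.5, Φ(−0.75/1.5 − 0.8416) = 0.090. At group level the values are 0.000 and 0.001. These hold whatever the size of the gain.

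**Placebo contrast with unequal intake.** Each hourly rating that is medicated after placebo but not yet after an active session moves the five-rating contrast by 1.5/5 = 0.3 points against hypoxia. Two such ratings cost 0.6 points, most of the 0.75 threshold.

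**The case against.** The strongest reply is that the rule speaks only of scores after treatment. Which of ten repeated ratings decide the verdict, and how post-dose ratings are handled, is ordinary content of an analysis plan, and a condensed article may leave it there. That stands in part: silence on rating times would not be a finding alone. But the article does fix a threshold, a baseline and a comparator, and applies them to every Likert outcome, including ratings whose medication state may differ from the baseline.

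Three stronger readings are tempting and are not supported.
- A reader might infer that the 1–5 h ratings decide the verdict. The article does not say so; it only fails to exclude them.
- A reader might infer that medication is always resumed within five hours. No section says when it restarts, and the urge item only suggests it. Supplementary Fig. 1, which holds the full measurement scheme, is not at hand. The exclusion of people likely to start dopaminergic treatment suggests that untreated people may be eligible, so the issue need not affect all 20.
- A reader might infer that dose times go unrecorded. An article cannot establish that.

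It is also fair to say that much of the harm comes from comparing with baseline rather than placebo. Every participant has two placebo sessions on the same schedule, and unstable dopaminergic dosing is an exclusion. A placebo contrast would remove the error under equal intake. Delayed intake after active sessions would hide benefit in that contrast rather than create it. The direct, 30 min and next-morning ratings are not exposed to this problem.

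**Conclusion.** The point holds conditionally: if the 1–5 h ratings enter the rule and usual dosing has resumed by then, a dose can be credited to hypoxia. With an assumed 1.5-point gain, no hypoxia effect and an SD of 1.0–1.5, a null protocol is called effective in about 20%, 30–35% or 45–59% of individuals, depending on whether all ten, the seven same-day or only the 1–5 h ratings are used. The group figures are about 20%, 70–88% and 99% or more. With OFF ratings alone they are 3–6% and about 0%.

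The top of the range should not be read as the trial's expected error rate. It requires the verdict to rest on the 1–5 h ratings alone, with the full gain in each, including the first. The gain and the SD are assumptions throughout.

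These are secondary outcomes of an exploratory study, but they carry its efficacy verdict. The change is worth making because unrecorded dose times cannot be reliably recovered afterwards.

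**What to change.** 1. State that the effectiveness verdict uses ratings made in OFF: direct and 30 min, with the three next-morning OFF ratings analysed separately.
2. Analyse the 1–5 h ratings only as active-minus-placebo contrasts, labelled supportive.
3. Record the clock time of each dopaminergic dose on session days, if this is not already done, and report time to first dose by condition as an outcome.
4. Keep any analysis restricted to pre-dose ratings, or adjusted for dose taken, as a sensitivity analysis. Dose timing may itself respond to treatment, and conditioning on it can introduce bias.
5. Align the hourly rating times in the text with Table 3.

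This concerns measurement and analysis only; how medication is managed on session days is for the sponsor. The cost is one field in the existing digital self-report and a few sentences in the analysis section. The downside is that the 1–5 h results, including the second window at about 3 h, become supportive only.
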